### 2.11. Interim Analysis

A group sequential design is utilized in this trial. Two equally spaced interim analyses will be performed at the end of the first and second years, respectively. Therefore, *α*-levels will be adjusted according the alpha-spending function approach in order to maintain the assumed 0.05 level for the overall study analysis. The primary purpose of the interim analysis is to determine whether the trial should be terminated early. The early terminated criterion is a statistically significant difference regarding the change of TNSS between participants receiving SHP and those receiving placebo patches at the adjusted significance level using an independent *t*-test or nonparametric tests. The first interim analysis will only analyze the difference between the SHP group and the placebo group. The second interim analysis, however, will analyze not only the difference between these two groups but also the difference between the placebo group and the waiting-list group which will have received five TSs of the SHP by the 2nd year. Independent statisticians who do not know treatment allocations will perform the interim analysis. Results of the interim analysis will be reported to the DSMC who will have unblinded access to all data. If the trial is terminated as a result of the interim analysis or by the recommendations of the DSMB, the final efficacy and safety analyses will be performed using the full dataset up until the interim end of the trial.

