### 2.6. Outcome Measurement

For the evaluation of the primary and secondary outcome measures, participants are required to complete two questionnaires, the Total Nasal Symptom Score (TNSS) and the Rhinoconjunctivitis Quality-of-Life Questionnaire (RQLQ), at the beginning of each of five TSs (from 2nd to 7th weeks) and at the 8th, 19th, 33rd, and 52nd weeks during each annual follow-up. In addition, participants are asked to complete diaries throughout the trial. The frequency of the ARAs is recorded and the use of RMs or other medications is documented in detail (Figure 1).

The primary outcome is the change of the TNSS from baseline to the end of the 52nd week. TNSS evaluates four nasal symptoms: nasal obstruction, sneezing, rhinorrhea, and nasal itch. The symptoms are self-assessed and recorded by participants, using a five-point scale (0 = no symptoms; 1 = mild symptoms; 2 = moderate symptoms; 3 = severe symptoms; 4 = very severe symptoms) [45]. The TNSS ranges from 0 to 16, with low scores indicating lighter nasal symptoms.

Secondary outcomes include (1) the change of RQLQ score from baseline to the 8th, 19th, 33rd, and the 52nd weeks; (2) response to interventions, defined as participants with a change in RQLQ score of ≥0.5 from baseline; (3) the frequency of ARAs; and (4) the use of RMs. The PE of the SHP is further explored based on the TNSS and RQLQ score between the placebo group and the waiting-list group at the end of the 1st year.

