### 2.9. Sample Size Calculation

We used a group sequential test to compare the SHP and placebo groups, hypothesizing a difference in the level of TNSS between SHP and the placebo. The sample size was calculated based on a mean change of 1.47 with a standard deviation (SD) of 2.9 scores in the SHP group and a mean change of 0.7 (SD: 1) scores in the placebo group [28]. We applied a 2 : 2 : 1 ratio to the SHP group, placebo group, and waitlist group, respectively. Considering a two-tailed significance level of 5% and a power of 80%, the sample size was 140 for the SHP group, 140 for the placebo group, and 70 for the waiting-list group. Assuming a dropout rate of approximately 20%, we will require a sample size of 174 for the SHP group, 174 for the placebo group, and 87 for the waiting-list group.

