### 2.10. Statistical Analysis

Statistical analysis will be performed in a blinded manner by qualified statisticians using PASW Statistic 18.0 (IBM SPSS Inc., Armonk, New York, USA) and SAS 9.2 software (SAS Institute Inc., Cary, USA). Missing data will be replaced according to the principle of multiple imputations. Two-tailed *p* values < 0.05 are considered to be statistically significant. Analyses will be performed for 2 populations: (1) an intention-to-treat population with all patients randomized and treated with at least one TS and (2) a per-protocol population including only patients with no major protocol deviations.

Demographic and clinical characteristics, as well as baseline data, will be presented to assess the baseline comparability of the three groups. Descriptive statistics will be presented for each group as the mean change (SD, 95% confidence intervals) or the percentage change in the outcomes from baseline to each time point. Differences in mean change from baseline to each time point will be compared between groups using analysis of variance. Comparisons between the two groups will be conducted using the superiority test based on the Bonferroni adjustment. For the analysis of factors affecting the outcome change in each time point, mixed-effects linear or logistic regression model will be performed adjusting for baseline characteristics and other variables. Safety will be evaluated by tabulations of AEs and ADRs and will be presented with descriptive statistics for each group. A chi-square test or Fisher's exact test will be used to compare the frequency difference of AEs and ADRs among the three groups. As cases are divided into different degrees of AEs and ADRs, a rank-sum test will be performed for analyzing the independently ordered multiple category data among the three groups.

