**Figure 2 fig2:**
[figure not shown]
Diagram of prescribed acupoints from the WHO Standard Acupuncture Point Locations in the Western Pacific Region in the SPAR^(1)^ study in 2014. ^(1)^SPAR: Sanfu herbal patch at acupoints for persistent allergic rhinitis.

**Table 1 tab1:** Dates and acupoints for each treatment session from 2014 to 2016 in the SPAR^(1)^ study.

		1st session	2nd session	3rd session	4th session	5th session
2014	Dates	8 July (Extra *Geng* day)	18 July (Initial *Sanfu*)	28 July (Middle *Sanfu*)	7 August (Final *Sanfu*)	17 August (Extra *Geng* day)
	Acupoints	BL13 (bilateral) BL23 (bilateral) BL21 (bilateral) BL14 (bilateral) CV12 GV14	BL15 (bilateral) BL19 (bilateral) BL42 (bilateral) EX-HN15 (bilateral) CV10 GV4	BL12 (bilateral) BL20 (bilateral) BL44 (bilateral) BL52 (bilateral) CV9 GV12	BL13 (bilateral) BL23 (bilateral) BL21 (bilateral) BL14 (bilateral) CV12 GV14	BL15 (bilateral) BL19 (bilateral) BL42 (bilateral) EX-HN15 (bilateral) CV10 GV4

2015	Dates	3 July (Extra *Geng* day)	13 July (Initial *Sanfu*)	23 July (Middle *Sanfu*)	2 August (Extra *Geng* day)	12 August (Final *Sanfu*)
	Acupoints	Adjusted only one week before treatments based on the traditional Chinese medicine theory				

2016	Dates	7 July (Extra *Geng* day)	17 July (Initial *Sanfu*)	27 July (Middle *Sanfu*)	6 August (Extra *Geng* day)	16 August (Final *Sanfu*)
	Acupoints	Adjusted only one week before treatments based on the traditional Chinese medicine theory				

^(1)^SPAR: Sanfu herbal patch at acupoints for persistent allergic rhinitis.

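### The three-look alpha-spending design treats year 1 as a third of the information, although the whole cohort has its week-52 outcome by then and the protocol does not say which year's week 52 is tested

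*Protocol article*

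**What the plan says.** - **Primary outcome (protocol article, section 2.6):** "The primary outcome is the change of the TNSS from baseline to the end of the 52nd week". The same section schedules a week-52 assessment in each annual follow-up and does not say which year's is primary.
- **Looks (section 2.11):** "Two equally spaced interim analyses will be performed at the end of the first and second years, respectively". Significance levels are adjusted by an unnamed alpha-spending function to hold 0.05 overall. The stopping criterion is a significant SHP-placebo difference in TNSS change, with no year attached.
- **Sample size (section 2.9):** "We used a group sequential test to compare the SHP and placebo groups". The input for the active arm is "a mean change of 1.47 with a standard deviation (SD) of 2.9 scores in the SHP group". For its comparator the plan takes a mean change of 0.7 with SD 1. The result: "Considering a two-tailed significance level of 5% and a power of 80%, the sample size was 140 for the SHP group", with 140 for placebo and 70 for the waiting list, raised to 174, 174 and 87 for 20% dropout.
- **Calendar (sections 2.1 and 2.5, Table 1):** five sessions a year on fixed dates, the first on 8 July 2014. The same participants repeat the cycle in years 2 and 3.
- **Significance convention (section 2.10):** two-tailed p "values < 0.05 are considered to be statistically significant".

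**The concern.** Equally spaced looks with alpha spending suit a trial in which information on one treatment effect builds up, usually because participants are still being enrolled or followed to the endpoint. Here nobody enters in years 2 or 3. If the primary outcome is week 52 of year 1, its information fraction at the first look is 1, not 1/3. If each look tests that year's change, the three tests concern effects after one, two and three courses in the same people. Their correlation is then whatever the between-year correlation is, not the value that the information fractions imply.

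Three things rest on this: the level at which the year-1 result is judged, the overall error rate and power claimed, and the decision to stop. The last is not easily undone, because section 2.5 has all groups receive SHP once the criterion is met, which ends the placebo comparison. If year 1 fails, the Discussion treats continuation as a further chance of significance, yet the protocol does not say on which outcome that success would count.

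**Working it through.** **Inputs (section 2.9).** Difference 1.47 − 0.70 = 0.77. Sum of variances 2.9² + 1² = 9.41. Two-sided alpha 0.05, power 80%, dropout 20%. Looks at the end of years 1, 2 and 3.

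**1. Reproducing the stated sample size.**
- Fixed design: n = 9.41 × (1.960 + 0.842)² / 0.77² = 124.6, so 125 per arm. This is not 140.
- Three looks at information 1/3, 2/3 and 1, by numerical integration: O'Brien-Fleming forms need 127 to 128 per arm, quadratic spending 131, Pocock forms 146, and linear spending (alpha × t) 139.19, so 140.
- Dropout under linear spending: 139.19 / 0.8 = 173.98, so 174. Half of that is 86.99, so 87.

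Of the rules tried, only linear spending at thirds of information returns 140, 174 and 87. The spending function is inferred from this match. Its limits are |Z| = 2.394, 2.294 and 2.200, or nominal p = 0.0167, 0.0218 and 0.0278. Overall power at 140 per arm under that assumed structure is 80.2%.

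**2. What the first look contains.** All 140 evaluable participants per arm have week 52, not the 140/3 ≈ 47 that the calculation counts. Noncentrality = 0.77 / √(9.41/140) = 2.970, and power ≈ P(Z > z − 2.970).

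| First-look rule | Critical z | Year-1 power, 140 per arm |
|---|---|---|
| Single test at two-sided 0.05 | 1.960 | 84.4% |
| Linear spending (implied by 140) | 2.394 | 71.8% |
| Pocock-type spending | 2.279 | 76% |
| Classical O'Brien-Fleming | 3.471 | 31% |
| O'Brien-Fleming-type spending | 3.710 | 23% |

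Keeping 80% at p < 0.0167 would take 167 per arm (209 with dropout).

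**3. Overall error and power with the implied limits.** The between-year correlation of the treatment contrast is not given. It is assumed equal for all pairs of looks and varied over its range. Power assumes that the 0.77 difference holds in every year.

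| Correlation | Type I error | Power to reject at any look |
|---|---|---|
| 0 | 0.065 | 98% |
| 0.3 | 0.063 | 95% to 96% |
| 0.5 | 0.058 | 93% |
| 0.7 | 0.051 | 89% |
| 0.9 | 0.040 | 84% |
| 1 | 0.028 | 78% |

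The last row also describes the other reading, in which year-1 week 52 is retested at every look. No data are added, so only the loosest limit (2.200) matters.

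**4. Calendar.** Section 2.6 places the five sessions in weeks 2 to 7. The first (8 July 2014) and fifth (17 August) are 40 days apart. Week 2 starts on day 8 and week 7 ends on day 49, so the first session is day 8 or 9. Day 364 is then 29 or 28 June 2015. Table 1 starts the 2015 sessions on 3 July, 4 to 5 days later.

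**The case against.** - **The later looks may not test different outcomes.** Correct: section 2.11 gives no year, so a reader may infer this but the text does not state it. The alternative, retesting year 1, also departs from the stated error and power. What is documented is that the year is unspecified and that neither reading fits the sample size.
- **Inflated type I error.** Tempting, but not supported. The direction depends on an unknown correlation: with the implied limits the error is above 0.05 at low correlation, close to it near 0.7, and below it beyond that.
- **An underpowered trial.** The 23% and 31% figures assume O'Brien-Fleming rules that the protocol does not name and that do not reproduce 140. Low power at an early look is also what such rules intend. Power to reject at some look exceeds 80% over most of the correlation range if the effect persists. The shortfall concerns the year-1 test on its own.
- **Section 2.10 contradicts section 2.11.** It does not. The 0.05 in section 2.10 reads as a general convention, and section 2.11 is the specific rule for the looks. A clarifying phrase is enough.
- **A stricter year-1 level is legitimate** if three annual chances of success are intended, and an analysis plan could derive limits from the actual correlation. Both points stand. Such limits would restore error control, but they would not raise the year-1 power or make section 2.9 describe this trial.
- **Timing is logistics.** Agreed. It bears on neither error nor power, and section 2.11 sets no deadline for data lock or committee review.

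**Conclusion.** The point holds in a limited form. The sample size and sequential scheme assume that information builds up in thirds, whereas a calendar-fixed cohort supplies all of its week-52 data in year 1. The protocol does not say which year's week 52 is primary or which is tested at each look. With 140 per arm and the implied limits, the year-1 test has 71.8% power, against 84.4% for a single test at 0.05 (23% to 76% under other common rules). Overall type I error is somewhere between about 0.065 and 0.028, and power to reject at any look between 98% and 78%. So 0.05 and 80% are not the properties of the design as described, but the documents do not show that the error is inflated or that overall power is low.

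These figures rest on the protocol's own means and SDs, on linear spending inferred from the match, on a common between-year correlation that is assumed, and, for overall power, on a 0.77 difference in every year.

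**What to change.** Name the year of the primary week 52 in section 2.6, and carry it through sections 2.9 to 2.11.

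- **If year 1:** test SHP against placebo once, at two-sided 0.05, when the last week-52 visit is in. Make year-2 and year-3 changes secondary, reported with confidence intervals and giving no further route to the primary claim. Restate section 2.9 as a fixed-sample calculation: 125 per arm needed (157 with 20% dropout), and 140 gives 84%. Cost: later years lose confirmatory status.
- **If annual looks remain routes to success:** state that each tests that year's change. Use an alpha split valid under any correlation, or limits computed from the actual between-year correlation, and restate the power in section 2.9. Cost: a stricter level at each look. An equal split (0.05/3 = 0.0167) leaves the year-1 test at 71.8% with 140 per arm.

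Either route changes wording and calculation, not visits. In section 2.10, add that p < 0.05 does not apply to tests with an adjusted sequential level. As a separate matter, reconcile the timing of the year-1 decision (week 52 ends about 28 to 29 June 2015) with the 2015 session dates in Table 1, which begin on 3 July.

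### Free improvement: the SHP–placebo tests use change in TNSS with no covariate, although adjusting for the baseline TNSS already collected would make the comparison more precise

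*Protocol article*

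**What the plan says.** **Outcome.** Section 2.6: "The primary outcome is the change of the TNSS from baseline to the end of the 52nd week". A TNSS of at least 3 is an entry criterion in section 2.2, so a baseline value exists for everyone.

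**Stopping test.** Section 2.11 makes the early-termination criterion a "statistically significant difference regarding the change of TNSS between participants receiving SHP and those receiving placebo patches", assessed at the alpha-spending level by "independent *t*-test or nonparametric tests". It names no covariate and does not say which of the two tests applies.

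**Between-group comparison.** Section 2.10: "Differences in mean change from baseline to each time point will be compared between groups using analysis of variance". It continues: "Comparisons between the two groups will be conducted using the superiority test based on the Bonferroni adjustment". The Bonferroni step deals with multiplicity; it does not bring in baseline TNSS.

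**Adjusted model.** Section 2.10 also plans that a "mixed-effects linear or logistic regression model will be performed adjusting for baseline characteristics and other variables". The stated purpose of that model is "For the analysis of factors affecting the outcome change in each time point". It is not named as the treatment test or as part of the stopping rule.

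**The concern.** A raw change score fixes the coefficient of baseline at 1, whatever the data show. When follow-up is less than perfectly related to baseline, that over-corrects and leaves avoidable noise in the treatment contrast. Fitting baseline TNSS as a covariate estimates the coefficient instead. With SHP and placebo allocated 1:1, this costs one degree of freedom and does not lose large-sample precision.

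The comparison matters because a positive interim result stops the trial (section 2.1), and section 2.5 then gives all three groups SHP, which ends the placebo comparison. The test carrying that decision should be a single named test and as precise as the collected data allow.

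**Working it through.** **Inputs.** From section 2.9: mean changes 1.47 and 0.70, SDs of change 2.9 (SHP) and 1 (placebo), two-sided 5%, power 80%, 140 evaluable per arm, 174 after dropout. Assumed, because the document does not give it: the baseline-to-follow-up correlation.

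**1. The plan's own figure.**
- Difference: 1.47 − 0.70 = 0.77.
- Sum of variances: 2.9² + 1² = 8.41 + 1 = 9.41.
- Fixed-sample n per arm: 9.41 × (1.96 + 0.84)² / 0.77² ≈ 124.6, so 125.
- Section 2.9 says a group sequential test was used. Three looks with linear alpha spending inflate n by 1.114: 124.6 × 1.114 ≈ 139, close to the stated 140. The spending function is not named, so this shows only that 140 is attainable.
- Dropout: 140 / 0.8 = 175, against 174 stated.

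The sample size uses the SDs of raw change. No baseline adjustment is built into it.

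**2. Unadjusted power at 140 per arm, fixed sample.** SE = √(9.41/140) = 0.259. Power = Φ(0.77/0.259 − 1.96) = 0.844.

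**3. Adjusted variance.** Let s be the baseline SD, shared by the randomised arms and equal to the follow-up SD within each arm. Let ρ₁ and ρ₀ be the baseline-to-follow-up correlations in SHP and placebo.
- Var(change) = 2s²(1 − ρ) in each arm. The SHP arm gives 2s²(1 − ρ₁) = 8.41 and the placebo arm 2s²(1 − ρ₀) = 1, so 1 − ρ₀ = (1 − ρ₁)/8.41.
- At 1:1 allocation the common ANCOVA slope is b = (ρ₁ + ρ₀)/2.
- Summed variance, ANCOVA: 2s²(1 − b²). Summed variance, change score: 4s²(1 − b). Ratio = (1 + b)/2.

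| ρ₁ (assumed) | ρ₀ (implied) | b | Variance ratio | SE at 140 per arm | Power |
|---|---|---|---|---|---|
| unadjusted | – | – | 1.00 | 0.259 | 84% |
| 0.3 | 0.92 | 0.61 | 0.80 | 0.232 | 91% |
| 0.5 | 0.94 | 0.72 | 0.86 | 0.240 | 89% |
| 0.7 | 0.96 | 0.83 | 0.92 | 0.248 | 87% |

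Power is Φ(0.77/SE − 1.96). The SE falls by about 10%, 7% and 4%. A simulation of this set-up (140 per arm, 20,000 runs per row) gave adjusted power of 91%, 89% and 87%, and type I error between 4.9% and 5.2%.

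**4. Sensitivity.** If the baseline SD is below the follow-up SD, which an entry threshold on TNSS could produce, the slope b moves towards 1 and the gain shrinks. At b = 1 the covariate adds nothing beyond the change score. With three looks all absolute powers are lower than in the table: under the linear-spending reading in step 1, the unadjusted figure is about the stated 80%, not 84%.

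**The case against.** **The plan is coherent as it stands.** The outcome is a change, the sample size is built on SDs of change, and the test is on change. The comparison is valid and powered for the test it uses. This stands in full, and it is why the point is an improvement and not an error.

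**Covariates and the choice of test may be in a statistical analysis plan that is not shown.** This stands in part. A condensed article need not list covariates. But it does name the deciding test, names it without a covariate, and gives the adjusted model another job. The document also does not say that the choice between a t-test and a nonparametric test is made after seeing the data; section 2.11 has statisticians blind to allocation do the interim analysis. The point is only that the choice is open on the page.

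**Adjustment is already planned.** It is, but not for the SHP–placebo decision. Its presence makes the change easy.

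Three stronger readings are tempting, and the document does not support them:
- A reader might infer that entry at TNSS ≥ 3 biases the change score through regression to the mean. The criterion applies to all arms, so under randomisation the effect is equal in expectation and cancels from the contrast.
- A reader might infer that ANOVA, the t-test or rank test, and the mixed model compete to be primary. Each has its own stated use, and for two groups ANOVA and the equal-variance t-test are the same test.
- A reader might apply one correlation to both arms, so that 0.3 gives a variance ratio of (1 + 0.3)/2 = 0.65 and power near 96%. With equal baseline and follow-up SDs, change SDs of 2.9 and 1 would then require baseline SDs differing 2.9-fold between randomised arms.

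**Conclusion.** The point holds as a free improvement. The test that decides early stopping, and the main between-group comparison, leave baseline TNSS unused as a covariate. The test used is valid and unbiased, so the cost is precision only, and the interim test is in addition stated as an unresolved alternative.

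Under the assumptions set out in the working, the variance of the SHP–placebo difference falls by roughly 8% to 20%, which is worth about 3 to 7 percentage points of fixed-sample power at 140 per arm. The direction is secure in large samples at 1:1 allocation. The size is not, because it rests on a correlation and on baseline SDs that the document does not report.

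**What to change.** In sections 2.10 and 2.11, before any unblinded look:

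1. Make one baseline-adjusted SHP–placebo contrast the deciding test at every look and at the final analysis: ANCOVA of TNSS with baseline TNSS as covariate, or the equivalent contrast from the mixed model.
2. Apply it at the same week-52 time point that the look's change score would use, and name the study year for each look. Week 52 recurs in each of the three annual cycles, so the week alone does not identify the value tested.
3. Keep the unadjusted t-test or rank test as a sensitivity analysis, and say which of the two it is.

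The sample size can stay as it is; any gain adds power. The cost is wording. Baseline TNSS is already collected, a baseline-adjusted model is already in section 2.10, and the software is already named there.

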Blinding offers significant advantages in the overall design of this study, as SHP is reported to have a potential PE [28]. In this trial, we blind the acupuncturists to the allocations by separating operational assistants who prepare the patches. This prevents the acupuncturists from being exposed directly to the labeled tubes filled with either SHP or placebo ointment. Although the placebo ointment is similar to the SHP ointment in appearance, it is difficult to imitate common skin irritations such as local redness, hotness, and/or blisters caused by SHP [17]. Therefore, it is a challenge to blind the participants, especially those who have experience with this treatment. However, skin reactions vary from person to person. To maintain blinding, participants will be asked to wait in a separate room. This will reduce the chances that they communicate with each other. In addition, the participating acupuncturists, assistants, nurses, and statisticians are all blinded to the allocations and instructed not to communicate with participants about the treatment reaction. Nevertheless, it must be pointed out that we cannot control the bias produced by the waiting-list group which is the open-label arm of this trial. Noncompliance from the waiting-list group may lead to a high dropout rate and/or loss of follow-up in the first year. To improve compliance, participants will be contacted by telephone, e-mail, or message before each visit point.

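### After year 1 the waiting list is on open-label SHP, yet it enters the second interim efficacy comparison and three-group tests that are not limited to year 1

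*Protocol article*

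**What the plan says.** Sections 2.1 and 2.5 of the protocol article give the waiting list no treatment in year 1 and the SHP group's treatment in years 2 and 3. Section 2.4 says this arm cannot be blinded, and the Discussion accepts that "we cannot control the bias produced by the waiting-list group which is the open-label arm of this trial". The primary outcome, TNSS, is rated by the participants themselves (2.6).

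Section 2.11 gives early termination as the main purpose of the interim analyses. The stopping criterion is a significant "difference regarding the change of TNSS between participants receiving SHP and those receiving placebo patches". The first interim compares SHP with placebo only. The second adds "the difference between the placebo group and the waiting-list group which will have received five TSs of the SHP by the 2nd year".

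Section 2.10 plans analysis of variance on change to each time point between groups, followed by Bonferroni-adjusted two-group comparisons. For safety, a chi-square or Fisher test "will be used to compare the frequency difference of AEs and ADRs among the three groups", and a rank-sum test compares their grades across the same three groups. None of these is limited to year 1. Only the placebo-effect analysis in 2.6 is tied to the end of year 1.

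**The concern.** The waiting list is a no-treatment control for one year and an open-label SHP arm for two. The tests in 2.10 and the second interim refer to it as a group without regard to that change.

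For efficacy, a year-2 difference between placebo and waiting list mixes three things: any effect of SHP, the effect on self-rating of knowing that one receives SHP, and the difference between one year on SHP and two years on placebo. These cannot be separated.

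For safety, a three-group test on data beyond year 1 has no clear reference: one arm has SHP exposure throughout, one has placebo exposure throughout, and the third has an untreated year followed by SHP exposure.

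The setting adds to the concern. The contrast sits in the section that governs termination, and the criterion there is worded by treatment received, not by randomised group. If the criterion is met, 2.5 moves all three groups to SHP, so the wording should admit one reading only.

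**Working it through.** **1. The plan's own figure, and whether it is touched.** Section 2.9 assumes "a mean change of 1.47 with a standard deviation (SD) of 2.9 scores in the SHP group". For placebo it takes 0.7 with an SD of 1. Alpha is 5% two-sided and power 80%. For a fixed design:

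n = (2.9² + 1²)(1.960 + 0.842)² / (1.47 − 0.7)² = 9.41 × 7.849 / 0.5929 = 124.6, so 125 per arm.

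The article names no spending function. Linear alpha spending over three equally spaced looks has an inflation factor of 1.117: 124.6 × 1.117 = 139.2, so 140, the stated number. Dividing by 0.8 for dropout gives 175 and 88, against 174 and 87 stated. The calculation concerns SHP versus placebo only and does not depend on this point.

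**2. Exposure at each look** (five sessions a year; none for the waiting list in year 1):

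| End of year | SHP | Placebo | Waiting list |
|---|---|---|---|
| 1 | 5 | 5 | 0 |
| 2 | 10 | 10 | 5 SHP |
| 3 | 15 | 15 | 10 SHP |

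SHP and placebo match in session counts throughout. The waiting list matches neither, and after year 1 it is no longer untreated.

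**3. Effect of an open-label shift on the year-2 contrast (illustration).** Inputs: 140 placebo and 70 waiting-list participants evaluable, placebo SD 1 (2.9). Assumed: no true SHP effect, a reporting shift b in the waiting list only, and a waiting-list SD of 1 or 2.9.

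SE = √(1²/140 + SD²/70), which is 0.146 for SD 1 and 0.357 for SD 2.9.

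Rejection rate at nominal two-sided 5% = 1 − Φ(1.96 − b/SE) + Φ(−1.96 − b/SE).

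| Assumed b (TNSS points) | SD 1 | SD 2.9 |
|---|---|---|
| 0.25 | 40% | 11% |
| 0.50 | 93% | 29% |
| 0.77 | about 100% | 58% |

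The largest shift equals the planned SHP versus placebo difference. An adjusted interim level would lower these rates but would not remove the bias.

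**4. The same shift in a three-group analysis of variance** (140/140/70, common SD, only the waiting list shifted): at b = 0.50 it rejects in 93%, 32% and 19% of trials for an SD of 1, 2.17 and 2.9.

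**5. Adverse events (illustration).** Assumed risk per session is 10% on SHP and 2% on placebo, independent between sessions, with no background risk. The share with at least one event after k sessions is 1 − (1 − q)^k.

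| End of year | SHP | Placebo | Waiting list |
|---|---|---|---|
| 1 | 41% | 10% | 0% |
| 2 | 65% | 18% | 41% |
| 3 | 79% | 26% | 65% |

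The waiting list moves from an untreated profile towards that of SHP, so the meaning of a three-group p-value depends on when the data are cut.

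**The case against.** **Stopping.** A reader might infer that the open-label comparison can stop the trial and so inflates the error rate. The documents do not support that. Section 2.1 ties stopping to SHP versus placebo, 2.9 describes the sequential test as comparing those two groups, and 2.11 lists placebo versus waiting list as a separate comparison without saying that it can trigger termination. If one nevertheless assumed that either comparison could stop the trial, two tests sharing the placebo arm (correlation 0.08 to 0.41) would raise the chance of a false signal at the second look from 2.2% to 4.2–4.4% at an assumed Pocock level, or from 1.4% to 2.7–2.8% at an assumed O'Brien-Fleming level. Neither the rule nor the boundaries are in the text, and Bonferroni splitting, which 2.10 plans for two-group comparisons without saying whether it applies at interims, would largely undo the increase. What stands is an ambiguity: at the second look, participants receiving SHP can be read to include the waiting list.

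**Safety.** A reader might also infer that the three-group tests would hide the patch's local reactions. That goes too far. SHP versus placebo has equal session counts, and 2.10 also tabulates events by group. How closely the waiting list comes to resemble SHP depends on whether risk accumulates over sessions.

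**Condensed article.** Reporting windows are often left to an analysis plan, so the missing period limit is partly silence. The analysis of variance sentence says only that groups are compared; that it covers all three is a close inference from its context. But the article does state a three-group adverse event test and does place the open-label contrast in the second interim, so these are not mere omissions.

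**Already disclosed.** The Discussion admits the open-label bias. That is disclosure; it does not change the planned analyses.

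**Conclusion.** The point holds as a limited one. Carried out as written on data beyond year 1, the plan yields an efficacy contrast open to expectation bias and unequal in treatment duration, and adverse event tests that mix untreated and SHP-treated time. The open-label status, the self-rated outcome, the second-interim contrast and the three-group adverse event tests are all stated in the article; the three-group efficacy test is inferred.

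The size of the bias is not known. The rejection rates of 11% to nearly 100% rest on assumed shifts of 0.25 to 0.77 points and assumed SDs, and the event shares rest on assumed per-session risks. Only the session counts come directly from the design.

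The randomised SHP versus placebo contrast, the first interim, the sample size and the year-1 placebo-effect analysis stand. On stopping, the documents support a request for clearer wording, not a claim of inflated error.

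**What to change.** In 2.11, state that only participants randomised to SHP versus participants randomised to placebo count towards the stopping criterion. Make the year-2 placebo versus waiting-list comparison descriptive and label it open-label.

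In 2.10, limit three-group tests of efficacy and adverse events to year 1, where they compare SHP, placebo and no treatment. For years 2 and 3, test SHP versus placebo only. Tabulate waiting-list adverse events separately for the untreated year and the SHP years. Because 2.10 defines the intention-to-treat population by at least one treatment session, also say in which analysis set waiting-list participants enter the year-1 tests.

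The cost is wording in two sections and a period split in the safety tables. No new data are needed and the sample size does not change. The one loss is that a year-2 comparison becomes descriptive.
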